#### Inclusion criteria

Parents’ education should not be in the fields of medical sciences and psychology.Mothers who have not previously been trained in adolescent sexual health education, child sexual abuse prevention, or sexual education courses.Mothers should be able to read and write.

#### Exclusion criteria

Unwillingness to continue cooperation during the trialFailure to receive 50% of the intervention for any reason

#### Research variables

In this clinical trial, the designed interventions are considered to be independent variables, and awareness, attitude, and mothers’ self-efficacy in the field of sexual health care of educable intellectually disabled adolescent girls are considered to be dependent variables.

#### Data collection methods

Questionnaires evaluating awareness and attitude, and mothers’ self-efficacy in the field of sexual health care of educable intellectually disabled adolescent girls are used in the quantitative phase of this trial. Researcher-made questionnaires are used for evaluation of mothers’ awareness and attitude. Reliability and validity of these questionnaires will be determined. Moreover, general self-efficacy questionnaire, introduced by Schwarzer & Jerusalem, is used for evaluation of mothers’ self-efficacy [32]. Mothers’ awareness questionnaire includes 23 questions with three options of “true, false, I do not know”. In measuring awareness score, one score will be given to the participants for each true answer. Minimum and maximum awareness scores are 0 and 23, respectively. Mothers’ attitude questionnaire includes 18 questions with a 5-point Likert scale of “strongly disagree, disagree, neither agree nor disagree, agree, and strongly agree”. Scoring is done from 0 to 4. Minimum and maximum attitude scores are 0 and 72, respectively. Self-efficacy questionnaire includes 10 questions with 4 options of “never true, rarely true, sometimes but infrequently true, and always true”. In measuring self-efficacy score, one score will be given to the participants for each true answer. Minimum and maximum self-efficacy scores are 0 and 10, respectively.

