#### Sample size

Sample size will be 27 participants in each group considering 95% confidence interval, 80% trial power, d = 2.9 for awareness, d = 11.3 for attitude, d = 5 for mothers’ self-efficacy, and 10% loss.

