## Discussion

Multiple researches indicate that intellectually disabled adolescents need a comprehensive sexual health care program in order to be protected from sexual abuse and harassment and their adverse consequences, such as unwanted pregnancy, illegal abortions, STIs, and HIV/AIDS [33–39]. Negative attitudes of teachers and mentors toward sexual education of intellectually disabled adolescents, cultural obstacles, parent’s awareness and attitude, and sexual taboos have limited the design and implementation of such kind of comprehensive programs and have caused inattention to sexual health care of intellectually disabled adolescents [22, 40–42].

Moreover, the researchers have supported studies carried out on education interventions of parents of intellectually disabled adolescents as a sexual health care strategy which will reduce sexual abuse and harassment consequences [22, 43]. According to the importance of sexual health care of intellectually disabled adolescents, the present study aims to design and implement a comprehensive sexual health care program for these adolescents. The framework of this program will improve awareness, attitude, and self-efficacy of mothers in the field of sexual health care. So they can help their girls to have healthy relationships, protect themselves in unhealthy situations, and prepare themselves for a healthy, safe, and socially accepted sexual life. This mixed methods study and its resulted intervention program should be able to improve sexual status of these adolescent girls and reduce the consequences of sexual abuse and harassment, malicious sexual behaviors in them, and consequently, improve social health. If this program works, it can become one of the leading education and care guidelines for sexual health care of intellectually disabled adolescent girls.

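### The third outcome is named as self-efficacy in sexual health care but is measured with a general self-efficacy scale, so its result cannot be read as the named outcome

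*Protocol article*

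**What the plan says.** Protocol article, Research variables, lists the outcomes. Awareness, attitude and "mothers’ self-efficacy in the field of sexual health care of educable intellectually disabled adolescent girls are considered to be dependent variables". The opening sentence of Data collection methods attaches the same field to self-efficacy, and the Discussion expects the program to "improve awareness, attitude, and self-efficacy of mothers in the field of sexual health care".

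Data collection methods then assigns the instruments. For two outcomes they are made for the study: "Researcher-made questionnaires are used for evaluation of mothers’ awareness and attitude", and their reliability and validity are to be determined. For the third, a published "general self-efficacy questionnaire" "is used for evaluation of mothers’ self-efficacy". It has 10 items with four response options, and its stated scoring is: "Minimum and maximum self-efficacy scores are 0 and 10, respectively".

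Sample size plans 27 mothers per group, using differences of 2.9 for awareness, 11.3 for attitude and 5 for self-efficacy, with 80% power and 10% loss. It does not say which scale the 5 comes from.

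**The concern.** The outcome is specific to one field and the instrument, by its own name, is not. Training aimed at one field can change a mother's confidence there without an equal change in her confidence in general.

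This matters for reading the trial in either direction. A null result could be reported as no effect on mothers' confidence in sexual health care, although that was not measured. A positive result could be reported as a gain in that confidence, with the same objection. Self-efficacy is one of only three outcomes and one of the three differences behind the sample size.

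The scoring of the scale (four response options reduced to one point per true answer) is a separate matter. Corrected scoring would still leave a general scale standing in for a specific outcome.

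**Working it through.** **Step 1. Construct against instrument (no arithmetic).**

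- Research variables, the first sentence of Data collection methods, and the Discussion all name self-efficacy in sexual health care.
- Data collection methods gives a general scale as the only self-efficacy instrument.
- Study-made questionnaires are limited to awareness and attitude. Nothing describes rewording the general items or checking them against the specific construct.
- The implementation method refers to self-efficacy without naming a field, so it neither adds to the conflict nor resolves it.

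The mismatch therefore stands on the text alone.

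**Step 2. Can the planned size be reproduced for this outcome?**

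Inputs from Sample size: difference 5, power 80%, 10% loss, and 5% significance from the 95% confidence level. Two-sided testing is my assumption. No SD is given, so 27 can only be solved backwards.

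- Evaluable mothers per group: 24, since 24 / 0.9 = 26.7, rounded up to 27.
- Implied SD = difference × √(n/2) / (1.960 + 0.842) = 5 × √12 / 2.802 = 6.18.
- The largest possible population SD on a 0 to 10 score is half the range, which is 5.

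An SD of 6.18 is not attainable on the stated score, so self-efficacy with a difference of 5 cannot be what fixes 27 per group. No usable SD for this outcome can be recovered from the sample size.

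**Step 3. Illustration of what might be lost.**

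Assumptions, none of them from the article: the general scale registers a fraction f of the planned 5 points; the SD is 2, 3 or 5; clustering of mothers within the six centers is ignored. Normal approximation, two-sided 5%:

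power ≈ Φ( 5f / (SD × √(2/24)) − 1.96 )

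For f = 0.5 the visible difference is 2.5 points, and √(2/24) = 0.2887:

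- SD 5: 2.5 / 1.443 = 1.73, and Φ(−0.23) = 41%
- SD 3: 2.5 / 0.866 = 2.89, and Φ(0.93) = 82%
- SD 2: 2.5 / 0.577 = 4.33, and Φ(2.37) = 99%

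| Fraction captured | SD 2 | SD 3 | SD 5 |
|---|---|---|---|
| 1 | >99% | >99% | 93% |
| 0.75 | >99% | 99% | 74% |
| 0.5 | 99% | 82% | 41% |
| 0.25 | 58% | 30% | 14% |

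Depending on two unknowns, the loss runs from negligible to severe.

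**The case against.** A general self-efficacy scale is a legitimate, published instrument, and using it avoids a third untested questionnaire. Awareness and attitude are measured with study-specific instruments, so the trial's evidence on its own topic does not rest on this scale. Self-efficacy is not designated as primary. All of this stands, and it limits the reach of the point. It does not remove the mismatch: a general scale is a sound choice for general self-efficacy, and the article names something else.

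A reader might go further and infer that the trial is likely to miss a real effect. One route is to solve 24 per group back to about 0.8 SD and multiply by an assumed correlation between general and specific self-efficacy. A t-test with 24 against 24 then has 77% power at 0.8 SD, falling to 48%, 27% or 13% for correlations of 0.7, 0.5 or 0.3. The documents do not support this reading, for four reasons:

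- With the planned 5 points, 0.8 SD needs an SD of about 6.2, which the stated 0 to 10 score rules out.
- A correlation between two scales across mothers is not the fraction of a treatment effect that carries over from one to the other.
- The content of the program is still to be settled through the qualitative phase, the literature review and the expert panel, so it cannot be assumed to act on the specific construct alone.
- If the 5 points came from this same general scale, the loss is already built in and would be counted twice.

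**Conclusion.** The point holds as a mismatch between outcome and instrument. Followed as written, the plan would report a result for a construct that it does not measure. That conclusion rests only on the article's own text.

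On missed effects, the documents support no more than this: the scale may miss an effect confined to self-efficacy in sexual health care. The size cannot be derived, because the SD, the overlap between the constructs and the source of the 5 points are all unstated. The figures of 41%, 82% and 99% at half capture illustrate the range and are not estimates. They also take the 5 points at face value, although that is half of the 0 to 10 range, and they ignore clustering. A smaller true difference or positive clustering would lower them.

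**What to change.** Either option is sufficient.

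**(a) Rename.** Call the outcome general self-efficacy in Research variables, Data collection methods and the Discussion, and withdraw the claim about self-efficacy in sexual health care. The implementation method carries no field-specific claim and needs no correction on this account. Cost: wording only.

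**(b) Measure the named outcome.** Add a short self-efficacy scale on sexual health care tasks, validate it alongside the awareness and attitude questionnaires, and keep the general scale as a supporting measure. The planning difference must be restated for the new score, with its SD and source. Cost: about ten further items in questionnaire work already planned, and slightly more burden for mothers. There is also a risk to weigh: items close to the taught content may favour the intervention groups, so they should be written with that in mind.

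The choice should be made before the first baseline questionnaire is completed, because the same instrument has to serve all three measurement times.

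### The self-efficacy scoring rule is undefined for a four-level response scale, and the planning difference of 5 fits the stated 0 to 10 range poorly

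*Protocol article*

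**What the plan says.** All places are in the protocol article, Third phase.

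- **Data collection methods, response format:** "Self-efficacy questionnaire includes 10 questions with 4 options of" graded frequency, from never true to always true.
- **Data collection methods, scoring:** "one score will be given to the participants for each true answer. Minimum and maximum self-efficacy scores are 0 and 10, respectively".
- **Data collection methods, the other two scales:** awareness has 23 true/false/don't-know items at one point each (0 to 23). Attitude has 18 items scored 0 to 4 by response level (0 to 72).
- **Sample size:** "Sample size will be 27 participants in each group", "considering 95% confidence interval, 80% trial power", with differences of 2.9 for awareness and 11.3 for attitude, and "d = 5 for mothers’ self-efficacy, and 10% loss". No SD, unit or scale is given for any of the three differences.
- **Research variables:** awareness, attitude and mothers' "self-efficacy in the field of sexual health care of educable intellectually disabled adolescent girls are considered to be dependent variables". The instrument named under Data collection methods is an existing general self-efficacy questionnaire.

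**The concern.** The self-efficacy scoring sentence repeats the awareness rule almost word for word. For awareness it works, because each item has a right answer. The self-efficacy items are graded self-ratings: nothing is right or wrong, and all four option labels contain the word true. A scorer cannot tell which responses earn the point.

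Self-efficacy is one of only three outcomes, measured before, immediately after and one month after the intervention in three groups. The scoring rule fixes every value that enters its analysis. If the cut is left open, it can be chosen after the data are seen. A difference of 5 on a ten-point scale also looks out of line with the other two planning differences, which raises the question of which scale it was taken from.

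**Working it through.** **1. Does the rule define a score?** Three 0/1 cuts are possible: count the top option only, the top two, or the top three. A mother who gives the second-highest option to all ten items scores 0 under the first cut and 10 under the second. The same form therefore yields either end of the range. The range itself follows from the rule (10 items × 1 point = 10); what fails is the match between the rule and the response format. Attitude shows no such problem: 18 × 4 = 72, as stated.

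**2. Planning difference as a share of the range.**

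| Outcome | Difference | Range | Share |
|---|---|---|---|
| Awareness | 2.9 | 23 | 12.6% |
| Attitude | 11.3 | 72 | 15.7% |
| Self-efficacy, as stated | 5 | 10 | 50% |
| Self-efficacy, four levels summed | 5 | 30 | 16.7% |

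The 30-point span is 10 items × 3 steps between the lowest and highest level.

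**3. What SD would give 27 per group?** The figure of 27 cannot be reproduced directly because no SD is stated, so I solved for the SD.

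- Inputs: 27 per group, 10% loss and 80% power from Sample size; 5% from the 95% confidence level; two-sided is my assumption.
- Evaluable: 27 × 0.9 = 24.3, so 24. Check: 24/0.9 = 26.7, rounded up to 27.
- Formula: n = 2 × [(1.960 + 0.842) × SD/d]², so d/SD = 2.802 × √(2/24) = 0.809.
- Implied SDs: awareness 2.9/0.809 = 3.59; attitude 11.3/0.809 = 13.97; self-efficacy 5/0.809 = 6.18.

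The first two fit their ranges. The third is tested next.

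**4. Largest SD on a 0 to 10 score.** For a group with mean m the variance is at most m(10 − m). The maximum is 25 at m = 5, so SD ≤ 5. If two means differ by 5, both cannot equal 5. The average of the two bounds is greatest at means 2.5 and 7.5, where each is 2.5 × 7.5 = 18.75, so the pooled SD is at most √18.75 = 4.33. An SD of 6.18 is out of reach.

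Other conventions for self-efficacy at 24 per group:

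| Convention | Implied SD |
|---|---|
| One-sided 5% | 6.97 |
| t-test instead of normal | 6.05 |
| Three-group ANOVA | 5.46 to 6.30 |
| t-test, Bonferroni 0.05/3 | 5.19 |
| t-test, Bonferroni 0.05/9 | 4.59 |

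All exceed 4.33.

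**5. Forward check on 0 to 10.** At the largest pooled SD, n = 2 × (2.802 × 4.33/5)² = 11.8, so 12 per group, or 12/0.9 = 13.3, so 14 with loss. With 24 per group the power for a difference of 5 is about 98% at SD 4.33 and higher at smaller SDs.

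**6. Forward check on a 30-point span (SD assumed).** SD 6.18 gives 24, or 27 with loss. SDs of 5 to 7 give 16 to 31, or 18 to 35 with loss. The largest SD possible on that span is 15.

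All figures ignore allocation by centre, for which the Sample size section lists no allowance.

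**The case against.** The strongest reply concerns the planning difference. One sample size is given for three outcomes. If 27 is the largest of three calculations, awareness or attitude may have set it, since their implied SDs fit their ranges. The SD used for self-efficacy is then unknown and the impossible-SD argument falls. That reply stands, and it makes steps 3 and 4 conditional. It does not explain why this difference alone is half of its range, though an ambitious difference is not in itself an error.

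A reader might infer that the two sections contradict each other outright, or that the outcome is under-powered. The documents support neither. A difference of 5 is arithmetically possible on 0 to 10. Power cannot be computed without an SD, and taken literally a 5-point difference would have at least about 98% power with 24 per group at an unadjusted 5%, ignoring clustering.

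It can also be said that the rule is incomplete rather than unusable, because a stated cut-point would yield a 0 to 10 score. That is correct, but no cut-point is stated, and any cut would throw away the grading that the mothers are asked to supply. Nor do the documents fix 10 to 40 as the right range; starting each item at zero, as attitude does, would give 0 to 30.

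**Conclusion.** The scoring rule is undefined as written. This rests on the text alone and needs no assumption: four ordered options, no keyed answer, no cut-point. An article may leave detail to a fuller document, but here it states a rule and a range, and the rule does not fit the response format.

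The poor fit of the planning difference is a conditional finding. The difference is 50% of the stated range, about three to four times the share for the other outcomes. If it was meant to produce 27 per group (24 evaluable, two-sided 5%, 80% power), the SD of about 6.2 cannot occur on 0 to 10 but can on a 30-point span. That suggests that planning used another scale; it does not prove it. No effect on the trial's sample size is demonstrated.

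A secondary point is that the outcome is named as self-efficacy in the girls' sexual health care while the instrument measures general self-efficacy. This has no bearing on the arithmetic.

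**What to change.** 1. In Data collection methods, delete the one-point-per-true-answer rule and the 0 to 10 range for self-efficacy. Score each item by its response level with consecutive integers and sum the ten items, as attitude is already scored. This gives a 30-point span, for example 0 to 30 or 10 to 40; the sponsor should state which.
2. In Sample size, state the SD and the scale behind the difference of 5, say which outcome determined 27, and restate the basis for self-efficacy on the scale to be analysed.
3. Name the outcome general self-efficacy to match the instrument, or reconcile the instrument with the domain-specific outcome in Research variables.

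The cost is a few sentences. The forms that the mothers complete are unchanged and no new data are needed, but the scoring should be fixed before any outcome data are examined. Only re-wording the items toward sexual health care would add work, because the scale would then need to join the validation planned for the two researcher-made questionnaires.

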#### The implementation method

The researcher will implement the designed program after obtaining permission from ethics committee of Isfahan University of Medical Sciences and the necessary coordination with authorities of The Ministry of Health and Welfare and The Ministry of Exceptional Education. This is done by referring to the centers covered by The Ministry of Health and Welfare and secondary exceptional schools and presenting a letter of introduction to the authorities of those centers regarding research objectives. After that, the researcher will be allowed to access to phone numbers of girls in secondary educational schools and centers covered by The Ministry of Health and Welfare, and call their mothers in order to explain research objectives and invite them to participate in the research. If the mothers are willing to cooperate, and have all the inclusion criteria, they will be selected by convenience sampling method with their informed consent. Mothers’ awareness, attitude, and self-efficacy will be considered as the suggested outcomes. Before intervention, the questionnaires will be filled by mothers in each of the three groups. Furthermore, the questionnaires will be refilled by mothers immediately and 1 month after the intervention.

#### Data analysis

The collected data will be analyzed by descriptive statistical methods (mean, standard deviation, minimum, and maximum), inferential statistics (paired t-test, Chi-squared test, Fishers exact test, ANOVA, Wilcoxon test, and Mann-Whitney test), and SPSS v20 software. ANCOVA will be used for adjusting intervening variables.

#### Integration of the qualitative and quantitative data

The results of the qualitative and quantitative phases of the study will be integrated and finally, a program for sexual health of educable intellectually disabled adolescent girls will be provided.

## Discussion

Multiple researches indicate that intellectually disabled adolescents need a comprehensive sexual health care program in order to be protected from sexual abuse and harassment and their adverse consequences, such as unwanted pregnancy, illegal abortions, STIs, and HIV/AIDS [33–39]. Negative attitudes of teachers and mentors toward sexual education of intellectually disabled adolescents, cultural obstacles, parent’s awareness and attitude, and sexual taboos have limited the design and implementation of such kind of comprehensive programs and have caused inattention to sexual health care of intellectually disabled adolescents [22, 40–42].

Moreover, the researchers have supported studies carried out on education interventions of parents of intellectually disabled adolescents as a sexual health care strategy which will reduce sexual abuse and harassment consequences [22, 43]. According to the importance of sexual health care of intellectually disabled adolescents, the present study aims to design and implement a comprehensive sexual health care program for these adolescents. The framework of this program will improve awareness, attitude, and self-efficacy of mothers in the field of sexual health care. So they can help their girls to have healthy relationships, protect themselves in unhealthy situations, and prepare themselves for a healthy, safe, and socially accepted sexual life. This mixed methods study and its resulted intervention program should be able to improve sexual status of these adolescent girls and reduce the consequences of sexual abuse and harassment, malicious sexual behaviors in them, and consequently, improve social health. If this program works, it can become one of the leading education and care guidelines for sexual health care of intellectually disabled adolescent girls.

## Abbreviations

AIDS: Acquired immune deficiency syndrome
HIV: Human immunodeficiency virus
IQ: Intelligence quotient
STIs: Sexually transmitted infections
